### Analysis in the larger set of all registered patients

We collect course of Hb levels during surgery (= day 0) or day 1, 2, 3 after surgery and the vital status at day 90 (all-cause mortality) for all registered patients.

The prognostic value of delta Hb (difference pre-op Hb and Hb on day three) and Barthel index on short term mortality will be analysed adding these factors to the generalised linear mixed model specified above.

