Exclusion criteria at registration comprise preoperative severe anaemia with Hb level < 9 g/dl, chronic kidney injury requiring dialysis, suspected lack of compliance with follow-up procedures, expected death within 3 months, participation in other interventional trials or previous participation in our trial, temporary inability to provide informed consent with absence of a legally authorised representative/legal guardian, and preoperative autologous blood donation. Additional exclusion criteria at randomisation exclude patients who experienced any component of the composite endpoint or received any allogeneic blood transfusion since registration.

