### Randomisation and Intervention

If Hb intra- or postoperatively reaches ≤9 g/dl (despite possible autologous transfusion) determined from blood samples mainly as part of the patient’s standard care at any time during surgery (=day 0) or day 1, 2, or 3 after surgery, registered patients will be randomised either to**LIBERAL group:** patients receive a single RBC unit each time Hb reaches ≤9 g/dl (≤ 5.6 mmol/l) with a target range for the post-transfusion Hb level of 9–10.5 g/dl (5.6–6.5 mmol/l), or**RESTRICTIVE group:** patients receive a single RBC unit each time Hb reaches ≤7.5 g/dl (≤ 4.7 mmol/l) with a target range for the post-transfusion Hb level of 7.5–9 g/dl (4.7–5.6 mmol/l).

The target post-transfusion Hb level needs to be reached within 24 h upon receipt of triggering lab result. The intervention per patient will be followed until hospital discharge or up to 30 days after surgery, whichever occurred first. Physicians will be allowed to refuse to transfuse, or transfuse patients irrespective of the group assignment in exceptional cases, e.g. hypervolaemia, symptomatic anaemia with physiological triggers of anaemic hypoxia, or massive/life-threatening bleeding, but must document the reason(s) in the study eCRF.

Central internet randomisation at the Clinical Trial Centre Leipzig uses block randomisation with variable block length stratified by centre. For urgent randomisation or in case of internet unavailability randomisation can be performed using sealed envelopes. Envelope randomisations will be checked during on-site monitoring.

All trial patients will receive standard perioperative care. The patients in both groups will not be exposed to additional risk since transfusion-strategy studies almost showed the same results. Hb transfusion thresholds used in previous studies varied from 7 to 10 g/dl for the restrictive and from 9 to 13 g/dl for the liberal group, respectively [5, 6, 15]. In addition RBC transfusion is the main treatment option for anaemia due to surgical blood loss. All patients benefit from intensive monitoring and consequently early detection of any decrease of Hb-level.

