### Statistical analysis

The full analysis set for the primary efficacy analysis will be as close as possible to the ideal implied by the intention-to-treat principle and includes all randomised subjects. A secondary per-protocol analysis of the primary outcome will be performed in all patients without major protocol violations.

Most endpoints will be analysed with scale-appropriate generalised linear mixed models adjusting for age, cancer surgery (y/n), type of surgery (intermediate- or high-risk), and incorporating centres as random effect. Further baseline clinical variables may be entered in secondary analyses.

For the primary endpoint, logistic regression will be used to estimate the treatment effect on the odds ratio scale with two-sided 95% confidence intervals provided. Secondarily, also point estimates and confidence intervals for the rate difference and the relative risk will be provided. The test of the null hypothesis that the odds ratio concerning the composite endpoint is equal to one will be tested using the Wald statistic for the coefficient of the treatment effect in the logistic regression.

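### The registered-cohort model enters the Hb fall without pre-operative Hb, so the delta-Hb coefficient mixes the size of the fall with the starting level

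*Protocol article*

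**What the plan says.** The section of the protocol article on the larger set of all registered patients plans one prognostic analysis: "The prognostic value of delta Hb (difference pre-op Hb and Hb on day three) and Barthel index on short term mortality". The two factors "will be analysed adding these factors to the generalised linear mixed model specified above". The model meant is the one under Statistical analysis, described there as "adjusting for age, cancer surgery (y/n), type of surgery (intermediate- or high-risk), and incorporating centres as random effect". Pre-operative Hb appears neither among its terms nor as an added factor of its own.

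Three other statements bear on the point.
- Statistical analysis also says: "Further baseline clinical variables may be entered in secondary analyses". It names no variable and commits to none.
- The exclusion criteria at registration rule out "preoperative severe anaemia with Hb level < 9 g/dl" and set no upper limit.
- Randomisation and Intervention gives the liberal group a "target range for the post-transfusion Hb level of 9–10.5 g/dl" and the restrictive group a "target range for the post-transfusion Hb level of 7.5–9 g/dl".

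**The concern.** Delta Hb is pre-operative Hb minus a later value, so it tends to be larger in patients who start higher. Two patients who are both at 9 g/dl on day three, having started at 10 and at 14 g/dl, have deltas of 1 and 5. The registration floor strengthens the link, because a patient entering near 9 g/dl has little room to fall. So do the target windows: among patients transfused into the same window, delta Hb is close to pre-operative Hb minus a constant.

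A larger delta therefore marks both a greater loss and a better start. If a better start goes with lower mortality, the two pull in opposite directions and one coefficient carries their sum. A reader could then take a fall to be less important prognostically than it is at a given starting Hb.

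**Working it through.** The plan states no figure for this analysis, so there is none to reproduce. The check is algebra followed by simulation.

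**1. The relation.** Let b_pre and b_fall be the log-odds of death per g/dl of pre-operative Hb and of fall when both are in the model. With pre-operative Hb left out, approximately

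b(stated model) = b_fall + b_pre × λ, where λ = cov(pre, delta) / var(delta).

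**2. Inputs.** From the document: the definition of delta, the 9 g/dl floor, the triggers (9 and 7.5 g/dl) and the two target windows. Assumed, because the document gives nothing: pre-operative Hb with mean 12.8 and SD 1.7 g/dl before the cut at 9; mean fractional loss 22%, with SD 10 percentage points; 90-day mortality about 4.5%; b_pre from -0.1 to -0.3; no other covariates.

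**3. λ without transfusion.** After the cut, pre-operative Hb has mean about 12.86 and variance about 2.67.
- cov = 0.22 × 2.67 = 0.59
- var(delta) = 0.22² × 2.67 + 0.10² × (12.86² + 2.67) = 0.13 + 1.68 = 1.81
- λ = 0.59 / 1.81 = 0.33

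With triggered patients moved into the target windows, simulation gives λ of about 0.61.

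**4. Fall adds nothing (b_fall = 0).**
- Without transfusion: exp(-0.1 × 0.33) = 0.97 and exp(-0.3 × 0.33) = 0.91.
- With transfusion: exp(-0.1 × 0.61) = 0.94 and exp(-0.3 × 0.61) = 0.83.

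**5. Fitted logistic models, 400,000 patients per setting.** Odds ratio per g/dl of fall in the stated model, for b_pre from -0.1 to -0.3:

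| True OR of the fall at fixed pre-operative Hb | No transfusion | Transfusion to target |
|---|---|---|
| 1.00 | about 0.97 to 0.91 | about 0.93 to 0.82 |
| 1.22 | about 1.18 to 1.09 | about 1.14 to 0.99 |

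A repeat run with the inputs above agreed to within about 0.01. With pre-operative Hb added, it gave 0.99 to 1.01 and 1.21 to 1.22. With b_pre = 0, the stated model returned the true value.

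**6. Dependence on the data model.** In a second simulation, day-three Hb was regressed on pre-operative Hb (slope 0.3 to 0.7, residual SD 1.0, pre-operative SD 1.6, mortality about 5%, 300,000 patients per setting). There λ was 0.59 to 0.78 without transfusion and 0.82 to 0.86 with it. For a pre-operative OR of 0.8 per g/dl (log-odds -0.22):
- A fall with no effect gave 0.84 to 0.87 without transfusion and 0.82 to 0.84 with it.
- A true OR of 1.2 gave 1.01 to 1.05 and 0.99 to 1.00. Adding pre-operative Hb restored 1.18 to 1.21.

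**7. When the sign reverses.** The stated coefficient falls below zero when the pre-operative OR is below exp(-b_fall / λ).
- First model, true OR 1.22 (b_fall = 0.20): exp(-0.20/0.33) = 0.55 without transfusion and exp(-0.20/0.61) = 0.72 with it.
- Second model, true OR 1.2 (b_fall = 0.18): about 0.74 at λ = 0.6 and 0.81 at λ = 0.86.

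**The case against.** The strongest reply is that this is one sentence about a side analysis, in an article that condenses a fuller protocol, and that the article lets further baseline variables be entered. A full protocol or analysis plan that is not shown may already include pre-operative Hb. That is possible. But the article states a specification here: it names both the added factors and the model that receives them, and the permissive sentence commits to nothing. The text as it stands can mislead.

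Second, the text asks about prognostic value, not about the effect of a fall at a fixed starting Hb. If delta Hb predicts survival partly because it marks a better start, that is a true association given the listed covariates. This stands as far as it goes, so the problem is one of interpretation and not of a false result. Pre-operative Hb is, however, known before surgery, and the useful prognostic question is what the fall adds to it. The stated model cannot answer that.

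Third, adding pre-operative Hb changes the question. Since b_pre × pre + b_fall × (pre - day three) = (b_pre + b_fall) × pre - b_fall × day three, the amended model is the model with pre-operative and day-three Hb. This is correct, and it is the question worth asking.

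A reader might infer more: that the plan will report a harmful fall as protective, or will produce a false positive finding at some given rate. The documents support neither. The distortion needs an association that they do not quantify, and it vanishes if there is none. Reversal of a true harm needs a strong association. No test or decision rule for delta Hb is stated, so no error rate can be attached. The larger distortions also depend on transfusion to target; in the first data model the effect is modest without it.

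**Conclusion.** The point holds as a weakness in how a secondary prognostic analysis is specified. The delta-Hb coefficient combines the fall with the starting level and is pulled downwards to the extent that higher pre-operative Hb goes with lower mortality. Under the first set of assumptions, a true odds ratio of about 1.22 is attenuated without transfusion. With transfusion to target it reaches about 1 only at the strongest association considered. The second data model gives a larger distortion, so the size should be read as illustrative; the direction follows from the definition of delta Hb.

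The size rests on assumed distributions of Hb and of blood loss, on an assumed association between pre-operative Hb and death, and on a model without the other covariates. The direction rests on that association being inverse, which fits the article's premise that anaemia harms elderly patients but is not quantified there. The randomised comparison, the primary endpoint, the sample size and the interim analysis are untouched.

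**What to change.** In the section on all registered patients, state that pre-operative Hb enters the mortality model as a continuous term alongside delta Hb or, equivalently, that pre-operative and day-three Hb enter as two terms. The delta-Hb coefficient then shows what the fall adds at a given starting Hb. If the full protocol or analysis plan already does this, one aligning sentence is enough.

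The cost is one covariate that must already be collected to compute delta Hb, with no change to conduct, data capture or sample size. The term does not deal with everything that shapes delta Hb: transfusion before day three and the assigned strategy also change it, and should be considered when the model is written out.

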### Clinical study monitoring

On-site monitoring follows a risk-adapted approach [31, 32]. Pre-study, initiation, regular, and closeout visits will be performed in all centres. The first regular visit takes place after discharge or day 30 after surgery of the first 3 randomized patients, the following visits will be performed after the discharge of additionally 15 more patients, but at least once a year. The intention of the visits will be to achieve high protocol compliance and data quality, as well as to ensure patients’ safety and rights.

Central monitoring will include a timely query management process based on consistency and plausibility checks combined with a dunning process for missing documentation. In addition, the trial biometrician performs statistical monitoring regularly in order to detect general and centre-specific problems in key study processes. Quality endpoints include accrual rate, rate of dropouts and protocol violations, promptness of randomisation when anaemia emerges, adherence to the assigned transfusion strategies, as well as timeliness of documentation.

## Discussion

The transfusion of allogenic RBC units is the standard procedure to treat peri- and postoperative severe anaemia. More than 50% of all RBC transfusions are used in old and frail patients, and current population dynamics in most developed countries will lead to an increasing demand for RBC transfusions [19]. Elderly patients have an increased prevalence of cardiovascular comorbidities and decline of functional reserves. Therefore, anaemia-related compensatory mechanisms are severely impaired in elderly patients, which may result in greater vulnerability to anaemia-related ischaemic events and perioperative complications [11, 12].

Here, the LIBERAL-Trial will provide a definite answer for this patient group whether a liberal transfusion strategy reduces the occurrence of major adverse events defined as the composite of all-cause mortality and severe ischaemic events within 90 days after non-cardiac surgery compared to a restrictive strategy.

Potential limitations might refer to cross-over between groups, needing to ‘register’ a large number of patients, lack of recruiting, and drop-out due to various protocol violations.

## Trial Status

Study protocol (V3.0) was finalised at 17th of October 2017. This trial was registered at https://clinicaltrials.gov/ct2/show/NCT03369210 (identifier: NCT03369210) at 12th of November 2017. Recruitment and enrolment of the patients started in January 2018, more than 200 patients have been registered and more than 100 randomised so far. The planned recruitment lasts 36 months.

## Abbreviations

AMG: Arzneimittelgesetz
BGA: blood gas analysis
eCRF: electronic case report form
GCP: Good clinical practice
Hb: haemoglobin
OCCR: overall composite complication rate
RBC: red blood cell
